**Methods:**

The AIM trial is a prospective, three-armed, phase II randomized controlled trial investigating the effects of a 16-week supervised circuit aerobic and resistance exercise (CARE) program versus a traditional aerobic and resistance exercise (TARE) program and attention control (AC) on adipose tissue inflammation in breast cancer survivors. 276 patients who are diagnosed with stage 0-III breast cancer, post-treatment, sedentary, and centrally obese are randomized to one of the three groups. The CARE and TARE groups participate in thrice-weekly supervised exercise sessions for 16 weeks. The AC group are offered the CARE program after the intervention period. The primary endpoint is adipose tissue inflammation assessed by core biopsy and blood draw. The secondary and tertiary endpoints are sarcopenic obesity, physical fitness and function, and patient reported outcomes. The exploratory outcomes are long-term breast cancer outcomes.

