#### 2.5.1 Primary Outcomes

##### 2.5.1.1 Adipose Tissue Chronic Inflammation

M1 and M2 phenotypes are the primary outcomes. As the M1/M2 system alone does not accurately represent the heterogeneity of adipose tissue macrophages (ATMs) in obesity (32), we also examine secretion levels of inflammatory cytokines to provide a comprehensive examination of the presence of chronic adipose tissue inflammation, which include interleukin (IL)-6, IL-8, tumor necrosis factor-α (TNF-α), high-sensitive c-reactive protein (hs-CRP), leptin, and adiponectin. Participants can volunteer to undergo an abdominal subcutaneous fat biopsy under local anesthesia performed by a certified physician assistant ([name]) and are asked to refrain from foods for 12 hours and anti-inflammatory pharmaceuticals for 3-5 days prior to biopsy. Participants lie supine on the examining table while the biopsy site is prepped and draped in a sterile fashion. Under ultrasound guidance performed by a licensed technician, a local anesthetic is injected into subcutaneous abdominal fat (midway between the iliac crest and umbilicus) after which a small skin nick is made. The core biopsy device equipped with a 13-gauge needle is inserted at the incision site.

Approximately 4 samples are taken from a single site, roughly a total of 40mg to 120mg of fat tissue. The biopsy is taken at the Brigham and Women’s Hospital and transported to the Immune Assessment Laboratory at the Center for Immuno-Oncology for processing. One sample is flash-frozen in liquid nitrogen and stored until RNA isolation, and the rest of the tissue is digested with a collagenase solution to create a single-cell suspension. Appropriate batch testing is conducted by research staff blinded to randomization.

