### 2.8 Sample Size

We anticipate recruiting 276 patients over a 48-month period and randomizing 92 patients to each arm of the study. Our hypotheses and analyses regarding our primary and secondary outcomes will reflect the comparison between CARE vs. TARE, and CARE vs. AC. Since the primary analysis involves two statistical comparisons, we will apply Bonferroni adjustment to control the overall type I error rate at 0.05 level. We estimated samples sizes for these two comparisons with each evaluated at two-sided alpha = 0.025. Our estimates of exercise intervention effect sizes were derived from randomized clinical trials (78–80) in addition to our preliminary data (81); most significantly, a study comparison of traditional endurance training vs. high-intensity circuit training (80) with effect sizes for outcomes common to our proposed trial (fat mass, lean body mass) was approximately 0.5-0.6. Effect sizes comparing exercise interventions to AC groups were larger, on 0.7-1.0. Our preliminary data compared exercise to AC (15 subjects per group), effect sizes were on the order of 1.0 (body composition measures) to 2.5-3.0 (inflammatory and other biomarkers) (81). The sample size determination was based on the comparison of the primary outcome between the CARE and TARE group because we expected that the difference between the CARE and AC group was larger than that between the CARE and TARE groups. We used an effect size of 0.5, two-sided alpha=0.025, and 80% power to estimate the sample size for comparisons of CARE vs. TARE, yielding a required 78 participants per group. To account for an anticipated 15% dropout rate, we will randomly assign 92 participants to each of the three groups. This will provide 80% or higher power to detect effect sizes of 0.5 and higher for other outcomes. For the optional biopsies, the sample size has been estimated at 50 participants per group based on our preliminary work (81). This will provide 80% power to detect a between-group difference, at a two-sided 0.025 alpha level, when the effect size is 0.9 for biopsy outcomes.

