The primary analysis would include all completed outcome assessments (regardless of whether the woman stayed on the intervention), inviting those who drop from the intervention to return for outcome assessments. The only missing data here would be those who drop the intervention and do not return for outcome assessments. Preliminary analyses will compare women who do and do not contribute to this analysis on baseline characteristics. Sensitivity/subgroup analyses will include (1): the receipt of chemotherapy as an established a-priori confounding factor due to possible chemotherapy-induced changes of chronic inflammation in adipose tissue (82–85), (2) multiple imputations of missing 2- and 4-month data (to evaluate the effect of missing data) (3); additional adjustment for baseline variables that differ between groups (to evaluate the effect of possible group differences on variables related to outcomes); and (4) adherence-based analysis, limiting subjects to those with at least 80% adherence (to estimate treatment effects under full adherence).

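### The 80% power at d = 0.5 with 78 per group does not apply to M1/M2, the named primary outcomes, which are planned in only 50 volunteers per group; the separate biopsy power statement is also inconsistent

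*Protocol article*

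**What the plan says.** Section 2.5.1.1 is explicit about the outcome: "M1 and M2 phenotypes are the primary outcomes". On how it is obtained, the same section says: "Participants can volunteer to undergo an abdominal subcutaneous fat biopsy under local anesthesia".

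The primary outcomes also reach beyond tissue. The abstract's Methods paragraph says "The primary endpoint is adipose tissue inflammation assessed by core biopsy and blood draw", and section 2.5.1.2 (Systemic Inflammation), on blood markers, falls under the Primary Outcomes heading.

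Section 2.8 describes the sizing as follows: "The sample size determination was based on the comparison of the primary outcome between the CARE and TARE group". The inputs are: "We used an effect size of 0.5, two-sided alpha=0.025, and 80% power to estimate the sample size for comparisons of CARE vs. TARE". This gives 78 per group, raised to 92 for 15% dropout. The supporting effect sizes of 0.5-0.6 for circuit versus endurance training are for fat mass and lean body mass.

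The section then treats biopsies separately: "For the optional biopsies, the sample size has been estimated at 50 participants per group based on our preliminary work". It claims 80% power for these at an effect size of 0.9 and the same two-sided 0.025 level.

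Section 2.9 says of the primary analysis: "The only missing data here would be those who drop the intervention and do not return for outcome assessments". It lists multiple imputation of missing 2- and 4-month values as a sensitivity analysis.

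**The concern.** If M1/M2 are the primary outcomes and about 50 of 92 women per group are planned to have a biopsy, 78 women per group cannot be evaluable for them. The headline power statement is therefore attached to an outcome for which the planned numbers do not deliver it. CARE versus TARE on adipose-tissue inflammation is the stated primary objective, so this is the comparison whose power readers will look for.

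The same section contains a second power statement, for biopsy outcomes, whose three figures (50 per group, d = 0.9, 80%) do not agree with one another. As it stands, section 2.8 contains no correct power statement for M1/M2.

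The missing-data sentence in section 2.9 has the same root. It fits an outcome measured in everyone. It does not fit one that 42 of 92 women per group (46%) are not expected to have at all.

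**Working it through.** **Inputs (sections 2.8 and 2.3).** Two-sided alpha 0.025 per comparison (Bonferroni, two comparisons), power 80%, d = 0.5 for CARE vs TARE, equal allocation, 15% dropout, 50 biopsies per group, d = 0.9 for biopsy outcomes.

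**Method.** Two-sample t-test (noncentral t), with noncentrality d·√(n/2) for n per group. The normal approximation is n = 2(z₀.₉₈₇₅ + z₀.₈₀)²/d², with z values 2.241 and 0.842.

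**Step 1: reproduce the plan's figure.**
- Normal approximation: 2 × (3.083)²/0.25 = 76.04, so 77. The t-test solution is 77.3, so 78, as stated.
- 78/(1 − 0.15) = 91.8, so 92, as stated.
- Power at 78 per group and d = 0.5 is 80.4%.

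The plan's calculation is thus an unadjusted two-sample t-test with 78 evaluable women per group.

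**Step 2: apply the same method to the planned biopsies.** If the 15% loss also applies to the 50 (an assumption), 50 × 0.85 = 42.5, taken as 42.

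| n per group | Noncentrality at d = 0.5 | Power at d = 0.5 | Power at d = 0.6 | d with 80% power |
|---|---|---|---|---|
| 78 | 3.12 | 80.4% | 93.0% | 0.50 |
| 50 | 2.50 | 59.0% | 76.4% | 0.62 |
| 42 | 2.29 | 50.6% | 67.9% | 0.68 |

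**Step 3: check the biopsy statement.**
- d = 0.9 with 80% power: the normal approximation gives 2 × (3.083)²/0.81 = 23.5, so 24; the t-test solution is 24.8, so 25 per group.
- At 50 per group and d = 0.9, power is 98.6%, not 80%.
- At 25 per group and d = 0.9, power is 80.4%.

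The stated d and power therefore fit 25 per group, which is 50 in total across two arms. If that is what was meant, power at d = 0.5 is about 30%.

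**Step 4: effect of the planned model.** Section 2.9 adjusts for baseline and uses two post-baseline times. The article gives no correlation, and the timing of the biopsies is in a figure not available here, so these values are assumptions (normal approximation, d = 0.5, 50 per group):
- One post-baseline measure, baseline-adjusted: power 65%, 74% and 81% at correlations of 0.3, 0.5 and 0.6.
- Two post-baseline measures, compound symmetry: 86% and 90% at correlations of 0.3 and 0.5.

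**Step 5: missing values.** 92 − 50 = 42, and 42/92 = 46% of each group without an M1/M2 value by design, before any dropout.

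**The case against.** Four points can be made for the plan.

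1. *The lower biopsy number is disclosed, with its own target of d = 0.9.* True, so the article does not claim 80% power at d = 0.5 for biopsy outcomes throughout. But the statement conflicts with attributing the 78 to the primary outcome, and its own figures do not agree.

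2. *Blood markers are also primary.* The abstract and section 2.5.1.2 support this, and the 78-per-group calculation can apply to them. Section 2.8 does not say which primary outcome it means, and section 2.5.1.1 names M1 and M2. The link has to be made explicit.

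3. *The mixed model will be more efficient than a t-test.* It may be, and with favourable correlations power at 50 per group could exceed 80%. The calculation behind the 78 takes no such credit, so the like-for-like figure is 59%.

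4. *The analysis set for biopsies may be in the full protocol or analysis plan.* That is fair for details of the set. It does not cover the missing-data sentence, which is wrong for M1/M2 as it stands.

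Two stronger readings are tempting and not supported. A reader might infer that the M1/M2 comparison is little better than chance. That combines an unadjusted test, an assumed loss from 50 to 42, and an effect of 0.5 that the article takes from body composition and does not assign to biopsy outcomes; it states no CARE vs TARE effect for M1/M2. A reader might also infer that women who declined biopsy will have M1/M2 imputed. Section 2.9 does not say so; it only fails to rule it out.

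**Conclusion.** The power statement in section 2.8 is wrong as written for M1/M2 and should be corrected. The arithmetic behind 78 and 92 is right, but it belongs to outcomes measured in all women. At the planned 50 biopsies per group, the plan's own method gives 59% power at d = 0.5, against the stated 80%, and 80% power only from d = 0.62. If 15% of the 50 are lost, the figures are 51% and d = 0.68.

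The biopsy sentence is separately inconsistent: either the 50 per group or the d = 0.9 with 80% power is misstated, and the article does not show which.

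These figures assume an unadjusted t-test, as in the plan's own calculation. The power of the mixed model cannot be determined without a correlation and the biopsy schedule. The conclusion concerns what the article claims and does not imply that the primary endpoint must change.

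**What to change.** **Section 2.8.**
- Tie the statement of 78 per group, d = 0.5 and 80% power to the primary outcomes measured in all women, that is, the blood markers.
- Confirm whether 50 is per group or the total for two arms, and whether it is before or after dropout.
- If 50 is per group, replace the biopsy sentence for M1/M2, CARE vs TARE, with 80% power at d = 0.62 and 59% at d = 0.5 (d = 0.68 and 51% if 42 remain).
- If 50 is the total for two arms, state 25 per group, 80% power at d = 0.9 and about 30% at d = 0.5.
- If credit is wanted for baseline adjustment or repeated biopsies, state the assumed correlation and the number of biopsies.

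**Section 2.9.**
- Correct the sentence on missing data so that it recognises women without a biopsy.
- Limit the M1/M2 analysis, and any imputation of it, to women with a pre-randomisation biopsy, so that membership of the set cannot depend on allocation.

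**Cost.** Wording in two sections, and a less favourable stated power for M1/M2. No extra participants or procedures are needed. Making a blood marker the sole primary endpoint would be a substantive change with its own trade-offs, and this correction does not require it.

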### 2.3 Randomization and Blinding

Upon the completion of baseline assessments, patients are randomly assigned to either CARE, TARE, or AC in an equal allocation ratio (1:1:1) using a permuted-block design with varying block sizes. The randomization is stratified by menopausal status (premenopausal and postmenopausal) which is evaluated at time of diagnosis. A study biostatistician ([name]) prepares the randomization schema prior to trial start-up, and the randomization allocation is provided to staff *via* a web-based application (REDCap) (24), and study investigators are blinded to the randomization process. The intervention allocation is not blinded to the study participants, interventionists, and outcome assessors due to the nature of exercise intervention.

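### The biopsy power statement does not reproduce: 50 per group, effect size 0.9, two-sided alpha 0.025 and 80% power cannot all hold

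*Protocol article*

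**What the plan says.** Section 2.8 (Sample Size) of the protocol article contains two calculations.

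- **Main comparison.** "We used an effect size of 0.5, two-sided alpha=0.025, and 80% power to estimate the sample size for comparisons of CARE vs. TARE". The result is 78 per group, and then: "To account for an anticipated 15% dropout rate, we will randomly assign 92 participants to each of the three groups".
- **Biopsy subset.** "the sample size has been estimated at 50 participants per group based on our preliminary work", followed by "This will provide 80% power to detect a between-group difference, at a two-sided 0.025 alpha level, when the effect size is 0.9" for the biopsy outcomes.

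The 0.025 level comes from a Bonferroni split of 0.05 over CARE vs TARE and CARE vs AC: "We estimated samples sizes for these two comparisons with each evaluated at two-sided alpha = 0.025". Section 2.3 allocates patients "in an equal allocation ratio (1:1:1) using a permuted-block design with varying block sizes", so each pairwise comparison has equal arms.

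Section 2.5.1.1 names the M1 and M2 phenotypes as primary outcomes and makes the biopsy that yields them voluntary. For the biopsy calculation, the article states no loss rate, no non-parametric test and no further alpha adjustment.

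**The concern.** For a two-group comparison of means with equal arms, any three of sample size, standardised effect, alpha and power fix the fourth. The biopsy sentences state all four, and they do not fit together: an effect as large as 0.9 with 50 per group should give power far above 80%.

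This is the only power statement specific to the biopsy subset, and that subset supplies named primary outcomes. Two things depend on which figure is wrong. The first is the recruitment target for an invasive, volunteer-only procedure: 3 × 50 = 150 participants over the three arms, or 3 × 25 = 75. The second is how a null CARE vs TARE result on the biopsy outcomes would be read, since the smallest effect detectable with 80% power is about 0.62 in one case and 0.90 in the other.

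**Working it through.** **Inputs, from sections 2.3 and 2.8.** n = 50 per group; standardised effect d = 0.9; two-sided alpha = 0.025; stated power 80%; equal allocation.

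**Method.** Two-sample t-test. Power is the probability that a noncentral t variable with 2n − 2 degrees of freedom and noncentrality d·√(n/2) exceeds the two-sided critical value in absolute size. The normal approximation, Φ(d·√(n/2) − z₀.₉₈₇₅) with z₀.₉₈₇₅ = 2.241, serves as a check.

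**Step 1: reproduce the plan's main figure.** With d = 0.5, alpha 0.025 and 80% power, the t-test needs 77.3 per group, rounded up to 78. Then 78 / (1 − 0.15) = 91.8, rounded up to 92. Both match section 2.8.

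**Step 2: apply the same method to the biopsy figures.** The noncentrality is 0.9 × √(50/2) = 4.5.

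- Normal approximation: Φ(4.5 − 2.241) = Φ(2.259) = 98.8%.
- t-test: 98.6%.

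The stated power is 80%, a gap of about 19 percentage points.

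**Step 3: solve for each figure, holding the others as stated.**

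| Held fixed (alpha 0.025 throughout) | Solved for | Result |
|---|---|---|
| 50 per group, d = 0.9 | power | 98.6% |
| 50 per group, 80% power | effect size | 0.625 |
| d = 0.9, 80% power | n per group | 24.8, i.e. 25 |

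**Step 4: can an unstated adjustment close the gap?** With d = 0.9, by t-test:

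| Variant | Power |
|---|---|
| 50 per group, two-sided alpha 0.0125 | 97.3% |
| 50 per group, two-sided alpha 0.025/6 | 93.8% |
| 50 per group, Mann-Whitney efficiency 0.955 or 0.864 | 98.2% or 97.0% |
| 42 per group (50 × 0.85 = 42.5, rounded down) | 96.6% |
| 17 per group (50 spread over three arms) | 61.0% |
| 25 per group (50 as a two-group total) | 80.4% |

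At 50 per group, two-sided alpha would have to fall to about 0.00025 (normal approximation) before power dropped to 80%. Of the readings of n that were tried, only 25 per group returns the stated power.

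**Step 5: power at the effect of 0.5 used to size the trial for CARE vs TARE.** 59% with 50 per group; 30% with 25 per group.

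**Step 6: rounding for a replacement sentence.** At 50 per group, 0.62 gives 79.4% and 0.63 gives 80.7%. At 42 per group, 0.68 gives 79.6% and 0.69 gives 80.8%. So 0.63 and 0.69 are the first two-decimal values that reach 80%.

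**The case against.** The strongest defence is that the sentence is safe as written. If 50 per group stands, the biopsy comparison has more than 80% power at 0.9, so the claim is met with room to spare. The randomised total of 276, the alpha split and the analysis model in section 2.9 do not depend on it. This largely stands: on the literal text the error is conservative, and the harm is a poorly stated detectable effect. But the sentence just before it, on other outcomes, explicitly claims power of at least 80%, whereas the biopsy sentence gives 80% at a specific effect. That reads as a design point, and as a design point it is wrong.

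A reader might infer that 50 is a two-group total mislabelled as per group, so that the true target is 25 per group and the biopsy comparison is badly underpowered for CARE vs TARE. The match at 25 per group is suggestive, but the document does not support the inference. It says 50 per group, attributes the figure to preliminary work that is not shown, and nowhere mentions 25. Nor need the sample size or the effect size be the wrong figure: the power may be misstated instead. An effect scaled by a different standard deviation (0.9/√2 ≈ 0.64, about 82% power) would also come close, but nothing in the text points to it.

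It would also go too far to say that no other power statement touches the primary outcomes. The 78-per-group calculation is described as resting on the primary outcome, and the abstract counts blood-based measures under the primary endpoint. The biopsy sentence is the only one specific to the biopsy subset.

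**Conclusion.** The inconsistency is real. With the stated inputs, power is 98.6%, not 80%; equivalently, 80% power goes with an effect of about 0.62 at 50 per group, or with 25 per group at 0.9. This rests on a two-sample comparison of means with equal arms, the method that reproduces the plan's own 78 and 92.

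Which figure is misstated cannot be settled from the document. If 50 per group is intended, power at 0.9 is understated and the smallest effect detectable with 80% power is overstated (0.9 against about 0.62). If 25 per group is intended, the stated biopsy target is double the true one. That second reading is only a possible explanation, and the 30% power at an effect of 0.5 depends on it. Any figure for 42 per group assumes that the 15% dropout, stated only for the main sample, applies to the biopsies too.

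**What to change.** Recalculate and replace the biopsy sentence so that sample size, effect size and power agree.

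- **If 50 per group is intended:** state 80% power for an effect size of about 0.63 at two-sided alpha 0.025 or, equivalently, about 99% power at 0.9. If the 15% dropout is assumed to apply to biopsies, say so and give about 0.69 with 42 per group. Note that power at the plan's CARE vs TARE effect of 0.5 is about 59% with 50 per group.
- **If 25 per group is intended:** correct the sample size, keep 0.9 and 80%, and note that power at 0.5 is about 30%.

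In either case, say whether the effect size refers to CARE vs TARE or to CARE vs AC. The cost is one recalculation and a short replacement text; the randomised sample size and the analysis model are unaffected.

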### 2.9 Statistical Analysis

Initial descriptive analyses will be used to evaluate baseline comparability among the three intervention groups, using ANOVA, or Kruskal-Wallis tests for continuous variables and chi-square tests for categorical variables. Unless otherwise specified, Statistical testing will be conducted at a two-sided 0.05 alpha level to determine statistical significance. For our primary and secondary outcomes, the variables used for the primary analysis will be the 2- and 4-month measurements of trial outcomes assessed during and at the end of the intervention period. Linear mixed-effects models will be used with the longitudinal data for the between-group comparisons, where two indicator variables for the treatment group (TARE, AC) relative to CARE, the baseline value of the outcome, and an indicator variable for measurement time (2-month/4-month) will be included as fixed-effects and subjects as random-effects in the models. With Bonferroni correction applied, the Wald test will be performed at 0.025 two-sided alpha level for each of the two comparisons regarding treatment effects (i.e., CARE vs. TARE, and CARE vs. AC); the between-group differences will be reported with corresponding 0.975 two-sided confidence intervals. Significant group differences will be followed by stratified analyses within measurement time (two and four months), and testing of group-time interactions, to evaluate treatment group differences within measurement time.

Post-intervention outcomes will be evaluated using the same linear mixed-effects models. The dependent variables will be the 8- and 12-month post-intervention measures, with the 4-month post-intervention measure, included as a fixed-effect.

The primary analysis would include all completed outcome assessments (regardless of whether the woman stayed on the intervention), inviting those who drop from the intervention to return for outcome assessments. The only missing data here would be those who drop the intervention and do not return for outcome assessments. Preliminary analyses will compare women who do and do not contribute to this analysis on baseline characteristics. Sensitivity/subgroup analyses will include (1): the receipt of chemotherapy as an established a-priori confounding factor due to possible chemotherapy-induced changes of chronic inflammation in adipose tissue (82–85), (2) multiple imputations of missing 2- and 4-month data (to evaluate the effect of missing data) (3); additional adjustment for baseline variables that differ between groups (to evaluate the effect of possible group differences on variables related to outcomes); and (4) adherence-based analysis, limiting subjects to those with at least 80% adherence (to estimate treatment effects under full adherence).

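### As described, multiple imputation will largely repeat the mixed model, so agreement between the two should not be presented as a test of what missing outcomes did to the result

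*Protocol article*

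**What the plan says.** All of this stands in section 2.9 of the protocol article unless another section is named.

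- **Primary model.** "Linear mixed-effects models will be used with the longitudinal data for the between-group comparisons". Besides the treatment indicators, "the baseline value of the outcome, and an indicator variable for measurement time (2-month/4-month) will be included as fixed-effects", with subject as a random effect.
- **Who is analysed.** "The primary analysis would include all completed outcome assessments (regardless of whether the woman stayed on the intervention"). Women who stop the intervention are invited back for assessment.
- **Where gaps come from.** "The only missing data here would be those who drop the intervention and do not return for outcome assessments".
- **What is planned about the gaps.** There are two items. The first is descriptive: "Preliminary analyses will compare women who do and do not contribute to this analysis on baseline characteristics". The second is among the sensitivity/subgroup analyses: "multiple imputations of missing 2- and 4-month data (to evaluate the effect of missing data").
- **The other listed analyses** concern chemotherapy, baseline differences between groups, and adherence ("adherence-based analysis, limiting subjects to those with at least 80% adherence (to estimate treatment effects under full adherence"). None of them addresses missing outcomes.

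The article states no missingness assumption, imputation model or auxiliary variables, and names no analysis that departs from missing at random. Section 2.8 anticipates 15% dropout.

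**The concern.** A linear mixed model fitted by likelihood to the available visits is valid if outcomes are missing at random given arm, baseline value and the visits that were observed. Standard multiple imputation built on those variables rests on the same condition and targets the same quantity. Comparing the two therefore checks little beyond simulation noise.

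The article gives the imputation a stated purpose, namely to show what missing data did to the result. Unless it brings in further information or a different assumption, it does not serve that purpose. Missing at random is also open to doubt here, because the article ties missingness to stopping the intervention, which is not in the model. If women who leave CARE and do not return have worse outcomes than retained women with the same baseline, both analyses would overstate the CARE effect by about the same amount. Their agreement could then be reported as robustness.

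**Working it through.** **1. The plan's own figures.** Section 2.8: "We used an effect size of 0.5, two-sided alpha=0.025, and 80% power to estimate the sample size".

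- Normal approximation: n = 2(z₀.₉₈₇₅ + z₀.₈₀)²/d² = 2(2.241 + 0.842)²/0.5² ≈ 76.0, rounded up to 77 per group.
- The t-test calculation gives 77.3, rounded up to 78, which is the plan's figure.
- Dropout: 78/(1 − 0.15) = 91.8, rounded up to 92, also as stated.

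The sample size reproduces and is not affected by this point.

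**2. Do the two analyses differ?** Simulation of two arms of 92, with 14 women per arm (14/92 = 15.2%) missing both post-baseline visits. The true difference is −0.5 on an outcome with SD about 0.95 per visit. There were 300 trials per scenario and 20 imputations each. With both visits either present or absent, the mixed-model estimate equals the baseline-adjusted comparison of the mean of the two visits. Selective dropout was placed in one arm only. The auxiliary variable stands for something like attendance.

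| Dropout mechanism | Imputation variables | No missing data | Mixed model | Imputation | Mean absolute gap |
|---|---|---|---|---|---|
| Completely at random | same as model | −0.498 | −0.500 | −0.499 | 0.008 |
| Completely at random | plus auxiliary | −0.511 | −0.511 | −0.513 | 0.022 |
| Depends on outcome | same as model | −0.502 | −0.607 | −0.607 | 0.007 |
| Depends on outcome | plus auxiliary | −0.497 | −0.603 | −0.572 | 0.035 |
| Depends on auxiliary | same as model | −0.499 | −0.573 | −0.573 | 0.009 |
| Depends on auxiliary | plus auxiliary | −0.499 | −0.580 | −0.499 | 0.081 |

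With the model's own variables, the gap between methods is as small when both are biased by about 0.1 (0.007) as when neither is (0.008). Agreement therefore does not separate the two situations. With a good auxiliary variable, imputation corrects partly or fully.

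**3. How large could the error be?** Let p be the missing fraction in an arm and δ the amount, in SD, by which its missing women do worse than missing at random predicts. Then

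true benefit = apparent benefit − (p_CARE·δ_CARE − p_TARE·δ_TARE).

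Take p = 0.15 (section 2.8), an apparent benefit of 0.50 SD, and δ_TARE = 0. The δ values are assumptions, since the article gives no outcomes for women who drop out.

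- δ_CARE = 0.25: 0.50 − 0.0375 ≈ 0.46
- δ_CARE = 0.5: 0.50 − 0.075 = 0.425, about 0.43
- δ_CARE = 1.0: 0.50 − 0.15 = 0.35
- δ equal in both arms with equal missingness: 0.15δ − 0.15δ = 0, so no bias

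**4. Tipping point, CARE-only shift.** With 78 observed per arm, the unadjusted SE is √(2/78) = 0.160 and the significance threshold at two-sided 0.025 is 2.241 × 0.160 = 0.359.

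- Observed 0.50: (0.50 − 0.359)/0.15 ≈ 0.94 SD
- Observed 0.40: (0.40 − 0.359)/0.15 ≈ 0.27 SD

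Baseline adjustment would lower the SE and raise both values.

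**The case against.** The strongest reply is that the article does not say how the imputation will be done. Imputation may include attendance or chemotherapy, which relaxes the assumption, or it may be run with shifts. Such detail commonly sits in a statistical analysis plan or full protocol that is not shown, and its absence is no finding. That stands. A reader might infer that the imputation cannot reveal anything, or that agreement is guaranteed. The document does not support either inference, and the last row of the table shows imputation with an auxiliary variable both removing the bias and exposing it.

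A reader might also infer that imputation is the only check. It is the only sensitivity analysis for missing outcomes, but a baseline comparison is planned too, and inviting women back reduces the problem at source. The comparison is descriptive and cannot detect differences in unobserved outcomes.

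Three further points stand:

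- The missing women are only those who leave and do not return, a subset of the 15%, so 15% missing is at or near the top of what is planned.
- The article does not say that these women fare worse, or that CARE and TARE dropouts differ. Both arms have one-on-one supervised sessions three times a week (section 2.4).
- The simulated setting omits women seen at 2 but not 4 months, whose 2-month value the mixed model would use. Nor does it describe the M1/M2 outcomes, where biopsy is optional and planned at 50 per group (sections 2.5.1.1 and 2.8).

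What survives is the mismatch between the stated purpose and the method as described.

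**Conclusion.** The point holds in a limited form and is a cheap improvement. As described, multiple imputation is the sole sensitivity analysis for missing 2- and 4-month outcomes. Unless it uses auxiliary variables or departs from missing at random, it will largely reproduce the mixed model. Agreement between the two should then not be reported as showing the effect of missing data, given the source of missingness that the article names.

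The size is conditional on 15% missing and a departure confined to CARE. At the planned effect it would take a departure of about 0.94 SD to lose significance, and about 0.27 SD at an observed 0.40 SD. It would be wrong to conclude that a CARE benefit would be an artefact of dropout. The article gives no dropout figures by arm, and equal departures cancel in CARE vs TARE. Neither the primary estimate nor the sample size is shown to be wrong.

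**What to change.** 1. Keep the multiple imputation, and include predictors of dropout that the trial already collects, such as session attendance in the exercise arms (section 2.5.5) and receipt of chemotherapy. State that it assumes missing at random given these variables.
2. Add a delta-adjusted tipping-point analysis. Shift imputed values toward no benefit over a stated range, for example 0 to 1 SD. Vary the shift separately by arm and include CARE alone, because an equal shift in CARE and TARE cancels in the comparison that sized the trial.
3. Report, for CARE vs TARE and for CARE vs AC, the shift at which the conclusion changes.
4. Apply the imputation and shifts only to measurements that were due for that woman. An optional biopsy that she did not volunteer for is not a missing value of this kind.
5. Fix these choices before outcome data are compared by arm.

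The cost is one extra imputation run and a table, with no new data. The reported robustness may look less favourable.
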